Evidence suggests that increasing guidance from a therapist can lead to greater adherence to online interventions, and result in improved outcomes [8, 12, 16, 23–26]. A facilitated discussion group delivered in the form of a bulletin board could provide a cost-effective and time-efficient means for increasing guidance from a therapist. Although more evidence is needed to support this hypothesis, there is some evidence of improved adherence to bulletin board support: Titov et al. [27], compared guided and nonguided Internet-based CBT for social phobia. The guided condition had access to a facilitated bulletin board and email contact from a therapist. The unguided condition had access to a nonfacilitated bulletin board. The study found that adherence rates for the supported condition were higher than for the unsupported condition (77% and 33% respectively). What was unclear from the study was the extent to which it was the facilitated bulletin board or the email support that successfully provided the additional therapist guidance.

A number of other studies [28–30] have also included discussion groups delivered in the form of bulletin boards as part of an online intervention but have failed to include the groups as a unique research variable so have been unable to identify the impact of the group on the effectiveness of the intervention.

In this study we will examine the effect of an online facilitated bulletin board on engagement with an online CBT-based stress management programme (WorkGuru) and explore whether effectiveness is mediated by engagement. We hypothesise that the bulletin board group will have better engagement outcomes than the minimal support group (MSG), and that these outcomes will result in decreased levels of psychological distress and increased levels of subjective wellbeing at work. Furthermore, we expect to identify moderating factors that influence levels of engagement and effectiveness that are either linked to the quality of the intervention (satisfaction, acceptability, credibility, system usability), time pressure, goal conflict, level of distress at baseline, or job autonomy.

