#### Primary and secondary outcome measures

The primary outcome measure of the study is engagement (the number of logins to the site); the secondary outcome measures include further engagement measures (the number of pages visited, the number of modules completed, and self-report engagement) and measures of effectiveness (the English language short-form version of the Depression, Anxiety, Stress Scale (DASS-21; [38]) and the wellbeing at work indicator (IWP Multi-affect Indicator; [39])). The DASS-21 has been designed to measure the negative emotional states of depression, anxiety and stress. In a review of the scale Henry and Crawford [40] reported a Cronbach’s alpha of .93. The scale was described as moderately sensitive to change in a clinical sample of depressed subjects [41]. The IWP Multi-affect Indicator is a 16-item measure of subjective wellbeing at work. Alpha coefficients for this scale range from .75 to .90 [42].

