Demographics will include: age, gender, fluency of written and spoken English, country of birth (UK, non-UK), relationship status, work role, number of working hours (low, middle, high), organisation, education level, income bracket and familiarity with online environment. The full list of measures is depicted in Table 3.

**Table 3 Tab3:** Measures

Measure (number of items)	T1	T2	T3
Primary measure: engagement			
Number of logins to the website		(X)	
Secondary measures: engagement			
Number of modules completed		(X)	
Number of pages visited		(X)	
Self-report engagement		(X)	
Secondary measures: effectiveness			
DASS-21 (21)	X	X	X
IWP Multi-affect Indicator (16)	X	X	X
Other measures			
Number of visits to discussion group		X^a^	
Number of contributions to discussion group		X^a^	
Existing psychological condition	X	X	X
Messages sent to and from coach		(X)	
Demographics	X		
Care as Usual (2)	X	X	X
Time Perception Index (5)	X	X	X
Goal conflicts (3)	X	X	X
Acceptability (6)	X	X	X
Credibility/expectancy (6)		2 weeks	
Level of importance (1)	X		
Negative effects of treatment (1)		X	X
Job autonomy (9)	X		
System Usability Scale (10)		(X)	
Client Satisfaction Questionnaire (8)		(X)	
Online Support Group Questionnaire (9)		X^a^	
Experience of stress management training (1)	X		
Sickness absence for stress-related complaint (1)	X	X	X
Contamination question (1)		X	X

T1 = baseline, T2 = 8 weeks (completion of intervention), T3 = 16 weeks (follow-up)

Groups: X = all three groups, (X) = MSG and discussion group, X^a^ = discussion group only

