### Statistical analyses

Analysis of the primary outcome measure (number of logins to the site) will be conducted on an intention-to-treat basis (participants’ data is analysed in the group that they are randomised to, regardless of treatment they receive or the extent to which they engage with the intervention). Analysis of the secondary measures (psychological distress and subjective wellbeing) will also be conducted on an intention-to-treat basis. Missing data will be imputed using the Last Observation Carried Forward method. For the engagement measures where no previous data is available, missing data will be imputed using the group mean. To check the robustness of the primary findings, sensitivity analysis including a per-protocol analysis will be performed. Per-protocol is defined as three or more logins to the WorkGuru site. This baseline has been identified from average login data from the site and reflects login data from other studies (for a summary of login data for online health promotion interventions see [23]).

Primary and secondary hypotheses will be explored using predominantly descriptive statistics. The means and/or medians (as appropriate) will be reported with standard deviations. Ninety-five percent confidence intervals will be calculated. Standardised effect sizes will be calculated using Cohen’s *d* and, where appropriate, odds ratios will be reported. Exploratory inferential analysis will be performed using *t* tests, analyses of variance (ANOVAs) and correlations as appropriate. In recognition that this is a pilot study caution will be taken in interpreting and reporting these results.

Baseline differences between groups will be explored using the chi-square test and ANOVA (as appropriate) and, where possible, we will compare demographics of trial participants with the workforce of each organisation to see if trial participants are representative of the workforce.

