The study by Hilvert-Bruce et al. [24] found that noncompleters still benefited from the intervention but that greater adherence resulted in greater benefit. Adherence to WorkGuru has been established at three logins to the site. This baseline has been established from current WorkGuru usage and in reference to login data from studies on other health promotion sites (see [23]). This pilot study will give a greater understanding of the extent to which participants are engaging with the intervention and will enable threshold levels of adherence to be refined.

One of the stated benefits of Internet-based or eHealth (the use of information and communication technology for health) interventions is that utilisation or dose can be objectively measured [59]. The most common objective exposure measure used in studies is login rates [23], other measures include number of pages visited, length of visit and sessions or modules completed. But to what extent do these measures accurately record engagement? Computer-based utilisation measures can register whether someone visits a page but not if they have meaningfully engaged with the material. Participants’ perception of their engagement may differ from the objective utilisation measure but it is not clear to what extent that is important. Is our perception of engagement or usage a better indicator of intervention exposure than an objective utilisation measure? This pilot study will help us to get a greater understanding of designing and interpreting utilisation measures, and a greater understanding of how that relates to outcome.

This study has two active groups (the MSG and the Discussion Group). While it is not possible to blind participants to the type of intervention that they receive, which could result in a bias in the self-reported measures, the inclusion of two active groups may limit this bias. A limitation of this study is that while it focuses on engagement the quantitative nature of the study does not allow exploration of why study participants may or may not engage with the intervention. A follow-up study using qualitative methodology is being planned to address this by gaining a greater understanding of the experiences of participants who failed to engage with the study, as well as of participants who did engage.

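### The per-protocol check on logins selects participants by their logins, so agreement or disagreement with intention-to-treat is not reliable evidence of robustness

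*Protocol article*

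**What the plan says.** All points are from the protocol article.

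- Primary analysis (Statistical analyses): "Analysis of the primary outcome measure (number of logins to the site) will be conducted on an intention-to-treat basis".
- Check on it (same section): "To check the robustness of the primary findings, sensitivity analysis including a per-protocol analysis will be performed".
- Definition of the set (same section): "Per-protocol is defined as three or more logins to the WorkGuru site". No other criterion is given, and nothing confines the set to the distress and wellbeing outcomes.
- Origin of the threshold (same section): "This baseline has been identified from average login data from the site". The Discussion uses the same figure as its adherence definition: "Adherence to WorkGuru has been established at three logins to the site".
- Expected direction (Background): the bulletin board group is hypothesised to engage better than the MSG.
- The wait list group has no access until after 16 weeks, so the login comparison is between the two active arms only.

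**The concern.** Whether a participant enters the check is decided by the value of the outcome being checked. Logins are counted after randomisation, and allocation is expected to change them. The people with three or more logins in the two arms are therefore not comparable by randomisation, and the comparison between them is not a cleaner version of the primary one.

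The cut is unlikely to fall in a harmless tail. It was taken from average site use, so it probably lies near the middle of the distribution. It could then remove a large share of participants, and unequal shares by arm if the board has any effect.

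At stake is how the pilot is read. A real effect on logins could be reported as not surviving its sensitivity analysis, or agreement between the two analyses could be taken as support that it does not give.

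**Working it through.** **The plan's own figure.** 3 arms x 30 = 90, which reproduces. The login comparison uses 2 x 30 = 60 of these. The article gives no login mean, SD, power or target effect for logins, so every distribution below is an assumption.

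**Assumed base case.** MSG logins are negative binomial with mean m = 3 and dispersion k = 1 (the geometric distribution). A mean of 3 is in keeping with a threshold taken from average site use.

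- Share kept: P(logins ≥ 3) = (3/4)³ = 0.422, or 12.7 of 30.
- Mean among those kept: 3 + 3 = 6.00, because the geometric distribution has no memory.
- Share below three: 0.578. It contributes 3 - 0.422 x 6 = 0.469 to the overall mean.

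**Case A: half of those below three become ordinary users with three or more logins.**
- Intention-to-treat (ITT) mean with the board: 0.422 x 6 + 0.289 x 6 + 0.234 = 4.50, against 3.00. Difference +1.50, d = 0.41.
- Per-protocol (PP): 6.00 against 6.00, d = 0.

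**Case B: half of those below three move to three or four logins (average 3.5).**
- ITT mean with the board: 0.422 x 6 + 0.289 x 3.5 + 0.234 = 3.78, against 3.00. Difference +0.78, d = +0.23.
- PP mean with the board: (2.531 + 1.012) / 0.711 = 4.98, against 6.00. Difference -1.02, d = -0.32.

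**Case C: the board multiplies mean logins by 1.5, with the same distributional form.**
- ITT: 3.0 against 4.5. Variance m + m² gives 12 and 24.75, so d = 1.5 / √18.375 = 0.35.
- PP: 6.0 against 7.5. Truncation at three leaves both geometric variances unchanged, so d is again 0.35. The ratio of means falls from 1.5 to 1.25, but a ratio is not a planned measure.

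| Case | ITT d | PP d | Kept of 30 (MSG, board) |
|---|---|---|---|
| A, 25% of low users moved | +0.21 | 0.00 | 12.7, 17.0 |
| A, 50% moved | +0.41 | 0.00 | 12.7, 21.3 |
| B, 25% moved | +0.11 | -0.19 | 12.7, 17.0 |
| B, 50% moved | +0.23 | -0.32 | 12.7, 21.3 |
| B, 75% moved | +0.36 | -0.40 | 12.7, 25.7 |
| C, ratio 1.5 | +0.35 | +0.35 | 12.7, 16.4 |

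**Range.** Case B with m = 3 or 4 and k = 1 or 2 reverses the sign every time (ITT d +0.07 to +0.39; PP d -0.12 to -0.40). Case C with m = 2 to 4, k = 0.5 to 2 and a ratio of 1.5 or 2 keeps PP d within 0.08 of ITT d, sometimes above it and sometimes below.

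**Simulation, 20,000 trials at 30 per arm, base case.** ITT is positive while PP is zero or negative in 38%, 63% and 80% of trials for case B (25%, 50% and 75% moved), and in 12% for case C.

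**Precision.** The approximate 95% half-width for d is 1.96 x √(2/30) = 0.51 with everyone. It is 1.96 x √(1/12.7 + 1/16.4) = 0.73 in the truncated set of case C.

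**The case against.** The best defence is that little hangs on this analysis. ITT on everyone randomised is primary. The word including leaves room for other sensitivity analyses. The statistics are mainly descriptive, inference is exploratory, caution is promised, and the Discussion says the pilot is underpowered for firm conclusions. All of that stands, and it limits the harm. It does not make a cut on the outcome a valid check of that outcome.

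The second line is that cases A and B are built to give their answers. That is fair: in A the zero is an input, and in B people are placed at or just above the threshold. Under a proportional shift, d hardly moves. A reader might therefore infer that the per-protocol result must erase or reverse a true effect, or that it carries no information at all. The documents support neither. They do not say how the board is expected to act: the hypothesis is better engagement, "We hypothesise that the bulletin board group will have better engagement outcomes than the minimal support group (MSG", and nothing states that the aim is to turn non-users into users. Weekly facilitated topics could equally produce more repeat visits. The cases show only that the answer depends on an unknown mechanism.

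A reader might also object that a discussion-arm participant who never opened the board still counts as per protocol. This is secondary. Three logins defines adherence to the programme both active arms share, and what is allocated is access to the board.

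Finally, one could read the per-protocol set as meant for distress and wellbeing. The sentence refers to the primary findings and the primary outcome is logins, so the text does not support that limit.

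**Conclusion.** The point holds as a fault in a stated rule. The set used to check the login result is defined by logins, after randomisation, on a variable allocation is hypothesised to raise. Depending on the mechanism, the per-protocol contrast can vanish (d 0.41 to 0), reverse (+0.23 to -0.32) or stay about the same (0.35 and 0.35). Agreement or disagreement with ITT is therefore not reliable evidence on robustness.

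The circularity rests on the text alone. The sizes rest on assumed negative binomial logins with an MSG mean of 2 to 4, and they illustrate what is possible without predicting what will happen. A reader might infer that a truncated d will feed the effect-size prediction for the definitive trial. The article does not say which analysis set supplies that prediction, so this is a risk to close off and not a stated plan. The change is worth making, but the primary analysis is not in question.

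**What to change.** - State that the three-login set will not be applied to logins, or to pages visited and modules completed, which depend on logins.
- For these outcomes, keep all randomised MSG and discussion-group participants.
- Report the proportion reaching three logins in each active arm as a binary engagement outcome, with a difference or odds ratio and 95% confidence interval. In case B above (50% moved) this would show 42% against 71%. It also serves the stated aim of refining the adherence threshold.
- Check the login result with a count model or a rank or median comparison, and with an alternative to filling missing engagement values with the group mean.
- Optionally, add a complier average estimate using the item "Number of visits to discussion group" in Table 3, as a separate exploratory estimand. State its assumption that allocation affects logins only through opening the board. It should not be the robustness check: it is the ITT difference divided by the share who visited the board, so it always has the ITT sign.

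Cost: one paragraph of wording, a little more analysis and no new data.

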### Recruitment and randomisation

Six UK-based organisations will be approached to participate in this study. A sample size of 90 study participants will be recruited from the participating organisations. The sample size of 30 participants per arm is based on the optimum number of discussion group participants identified by WorkGuru, and is equal to the medium per arm sample size identified in an audit of sample sizes for pilot and feasibility studies [32]. Participants will be recruited through advertisements distributed via email, the organisations’ intranets and in-house magazines. All marketing information will include an email address inviting people who are interested in participating in the study to access information made available online or by emailing the first named author (SC). An information leaflet and a link to the online screening questionnaire, the short-form version of the Perceived Stress Scale (PSS-10; [33]) will be made available to all people who express an interest in the study. People who meet the inclusion criteria will automatically be sent a link to the online baseline questionnaire. The online questionnaires will be designed and distributed using Qualtrics survey software. Participants who complete the baseline questionnaire will be randomised. The first author will create an allocation schedule using a computer-generated randomisation sequence (random.org). An independent researcher not otherwise involved in the research will allocate each group (A, B or C) as an active condition (with or without a facilitated bulletin board) or as the WLC. Participants will be randomly allocated on a ratio of 1:1:1 to these groups. The study researchers will be blind to the group allocation.

Randomisation is being conducted at an individual level rather than at organisation or team level. This allows us to control for group stressors such as large-scale redundancies and team deadlines. One of the risks of individual-level randomisation is contamination between the groups (i.e. participants in the WLC talking with participants in an active intervention). The extent of contamination between the study groups will be monitored.

Participants using the bulletin board will be required to use a pseudonym to maintain researcher blindness. Individual-level randomisation has been chosen to control for group stressors (i.e. organisational, department or team change).

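### No baseline-adjusted estimate is stated for DASS-21 and IWP; ANCOVA on the T1 score would sharpen these secondary effect sizes and protect them from chance imbalance

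*Protocol article*

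**What the plan says.** Table 3 of the protocol article schedules DASS-21 and the IWP Multi-affect Indicator at T1 (baseline), T2 (8 weeks) and T3 (16 weeks) for all three groups. Both are secondary outcomes.

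The Statistical analyses section sets the tone with "Primary and secondary hypotheses will be explored using predominantly descriptive statistics". It then says "Ninety-five percent confidence intervals will be calculated" and gives Cohen's d as the standardised effect size. Exploratory inference is by t tests, "analyses of variance (ANOVAs) and correlations as appropriate". On baseline it says: "Baseline differences between groups will be explored using the chi-square test and ANOVA (as appropriate"). It names no covariate, ANCOVA, change score or repeated-measures model.

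On size, Recruitment and randomisation says: "The sample size of 30 participants per arm is based on the optimum number of discussion group participants identified by WorkGuru". Predicting an effect size for the definitive trial is one of the four objectives under Aim of the study.

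**The concern.** A T1 score on the same scale is usually the best available predictor of the T2 and T3 scores. The trial collects it from everyone, but the stated analyses do not use it to adjust the treatment comparison.

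Testing baseline differences is no substitute. Under randomisation the null hypothesis of such a test is known to be true. With 30 per arm the test also misses imbalances large enough to matter, and whatever its result, the estimate stays the same.

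What is at stake is the quality of the DASS-21 and IWP effect sizes and their 95% intervals, which may be carried into planning the definitive trial.

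**Working it through.** **Inputs from the protocol article.** There are 30 participants per arm in three arms, and 3 × 30 = 90 reproduces the stated total. No power calculation is given, so there is none to reproduce. Intervals are at 95%, taken as two-sided.

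**Assumptions.** The T1-T2 correlation r is not given, so I use 0.3, 0.5 and 0.7. I also assume equal SDs at both times and all 30 per arm analysed. Everything is in SD units.

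**Unadjusted comparison of post scores, two arms.**
- SE = √(2/30) = 0.258
- 95% half-width = 1.96 × 0.258 = 0.51

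**Formulas.**
- ANCOVA: SE = 0.258 × √(1 − r²). Equivalent unadjusted size per arm = 30/(1 − r²).
- Change score (the same contrast as a group-by-time ANOVA with two time points): SE = 0.258 × √(2(1 − r)).
- Shift in the estimate from a baseline imbalance of 0.3 SD: 0.3 × r for post scores, 0.3 × (r − 1) for change scores. ANCOVA removes it.

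| r | ANCOVA SE | ANCOVA half-width | Equivalent n per arm | Change-score SE | Shift, post score | Shift, change score |
|---|---|---|---|---|---|---|
| 0.3 | 0.246 | 0.48 | 33 | 0.306 | 0.09 | −0.21 |
| 0.5 | 0.224 | 0.44 | 40 | 0.258 | 0.15 | −0.15 |
| 0.7 | 0.184 | 0.36 | 59 | 0.200 | 0.21 | −0.09 |

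**How likely is such an imbalance?** The chance baseline difference between two arms has SD √(2/30) = 0.258. It exceeds 0.3 SD with probability 25% for one pair of arms, and 48% for at least one of the three pairs. A pairwise 5% test would flag only differences above about 1.96 × 0.258 = 0.51 SD, so a 0.3 SD imbalance would normally pass unremarked.

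**Simulation check.** I used 20,000 two-arm trials of 30 per arm at each r, with no treatment effect. The empirical ANCOVA SEs were 0.249, 0.225 and 0.188, slightly above the formula because the slope has to be estimated. The post-score SEs were 0.258, 0.256 and 0.260. All mean estimates lay within 0.004 of zero, so none of the three methods is biased over repeated randomisations.

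**One cost, not two.** The imbalance noise is already inside the unadjusted SE. At r = 0.5, (0.5 × 0.258)² + 0.224² = 0.017 + 0.050 = 0.067 = 0.258². The wider interval and the sensitivity to imbalance are two views of the same loss and must not be added.

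**The case against.** The strongest reply is that the article leaves the form of the ANOVA open. A group-by-time ANOVA would use T1, and details of covariates may sit in a fuller plan. That is fair as far as it goes: the correct statement is that no adjustment is stated, not that adjustment is ruled out. But the open wording does not rescue the plan. The two-time-point version of that ANOVA is a change-score analysis. It also leaves chance imbalance in the estimate, with the opposite sign, and is less precise than ANCOVA at every r examined.

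It can also be said that these are exploratory analyses of secondary outcomes in a pilot that calls itself underpowered, and that the effect-size objective does not name an outcome. The effect-size example in the Discussion concerns adherence. This limits the weight of the point but does not remove it, because d and its interval will be reported for these scales.

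The gain depends on r. At 0.3 it is small: a 9% reduction in variance. Selection on PSS-10 ≥20 may narrow the baseline range and lower r.

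Three stronger readings are tempting, and the document does not support them.
- **T1 is used only in baseline tests.** It is not. Baseline distress is a possible moderator, T1 is the value carried forward when later scores are missing, and pre-post deterioration is to be reported (instrument not named). None of these adjusts the treatment effect.
- **A baseline imbalance passes in full into d.** For observed post scores it enters multiplied by r.
- **The plan contradicts itself on organisation.** Of individual randomisation the article says "This allows us to control for group stressors such as large-scale redundancies and team deadlines". That is a reason for randomising individuals rather than teams, and such randomisation balances group stressors in expectation without a covariate. There is no contradiction.

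**Conclusion.** The point holds for DASS-21 and IWP only. No baseline-adjusted estimate is stated, and the one stated step on baseline differences does not correct them. The loss is one of precision and of sensitivity to the imbalance that happens to arise. It is not systematic bias.

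At 30 per arm, adjustment would cut the 95% half-width from 0.51 SD to between 0.48 and 0.36 SD for r between 0.3 and 0.7. It would also remove a shift of 0.09 to 0.21 in an unadjusted post-score d when the baseline imbalance is 0.3 SD. These figures rest on an assumed r, equal SDs over time and complete data; attrition would widen every interval.

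The primary analysis of logins has no baseline value and is untouched. This is an improvement worth making because it is free; it is not a defect that undermines the trial.

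**What to change.** State in Statistical analyses that between-group differences in DASS-21 and IWP at T2 and at T3 will be estimated by ANCOVA with the T1 score of the same scale as covariate. Report the adjusted difference with its 95% CI, and compute the standardised effect size from that difference. Name the SD used as divisor; it should be an SD of the raw scores, because the model's residual SD would put d on a different scale. Replace the chi-square and ANOVA tests of baseline differences with a descriptive table by arm.

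The cost is a change of analysis wording and one degree of freedom per model. No new data, visits or participants are needed. The analysis of logins stays as it is.
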